Fernandez et al published a review of diagnostic studies to test pH of aspirate fluids using a litmus paper; in this way they evaluated if the NGT has been placed into the stomach. It has been noted that the color variation could be reduced based on the gastric pH, thus the litmus paper is not considered as sufficiently sensitive (17). A recent clinical trial by Gilbertson et al identified the cut off pH<5.5 to distinguish between the correct positioning in the stomach (20). A study was published by Bercik et al and by Tobin et al in which it was planned to use a magnets to locate and assist the positioning of the SNG (4, 62).

The study documents the accuracy and sensitivity of using a permanent magnet and an external computer to confirm the placement of the NGT in healthy patients. It is an expensive procedure that could not be applied in patients that perform MRI.

It is important to consider that actually the ultrasound methodology results as the most effective procedure, but it presents many limits, between them it requires a specific know how and an ultrasound scanner always available and finally it has a low sensitivity.The medical practice, according to the literature, takes into consideration the following values: etCO2 trachea mean value is 40 mmHg (range 35-45 mmHg) and etCO2 esophagus <25mmHg; pH stomach mean value 3.8 (range 3.2-4.4) and pH esophagus 8.5 (range 6-9.5).

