## 3.2 Project rationale and significance

Through the use of methods already adopted in clinical field, we want to collect the values of the etCO2 from the trachea and the pH when the NGT is well positioned in stomach. . There are two methods, already present at clinical level but that need to be implemented: the capnometer and the pH-meter.

The use of the graphic capnometer (capnography) has already been demonstrated to be useful for detecting the positioning of the NGT at the tracheal level (7, 33, 61, 27, 18), even if today there are no studies able to show what is the "threshold level" of the detected CO2 to say with high specificity that NGT is certainly found in the airways (25-27, 31, 33-35, 37, 44, 46, 58-59, 61).

Furthermore, the use of the pH meter has already been remarkably demonstrated to be useful in analyzing the different pH levels in the proximal gastro-enteric tract, with differences between the stomach and the esophagus, even if there are no studies in this sense to identify the "threshold level" below which the pH certainly appears to be a gastric and non-esophageal pH (41-43, 50, 52, 60).

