# Study OBJECTIVES and Design

## 4.1 Primary and secondary endpoints

The primary endpoint is to identify the threshold value in the distribution and in the frequency of etCO2 and pH values. The pH values will be compared with the performed X .

The threshold values for etCO2 and for pH will be determined in two groups: group A, with the aim to find a threshold value of etCO2 above which we can be sure that aspiration probe is in the trachea and group B, with the aim to find a threshold value of pH below which we can be certain that NGT is in the stomach.

Further secondary results are expected:

- for patients in group A it will be necessary to perform a sub-analysis for the threshold value in the group of patients suffering from COPD;

- for patients in group B, a sub-group analysis will be performed for the threshold value for patients taking proton pump inhibitors (PPIs), and / or in the presence of an already diagnosed gastro-esophageal reflux disease.

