## 4.3 Study intervention

Group A procedure:

Patients needing the installation of a NGT at the Clinica Luganese Moncucco are consecutively enrolled and selected according to the inclusion and exclusion criteria listed below. The enrolled patients, after receiving adequately protocol study explanation and signed the informed consent, are sedated and intubated according to the clinical indications and the local protocols, independently from the ongoing study.

Anaesthesia is performed by a professional anaesthesiologist and an anaesthetist nurse, using standardized procedures according to local routine protocols. Induction and intubation therefore take place independently of the ongoing clinical study, independent from both indications for intubation, the choice of drugs and intubation material. At the end of the procedure, as usual, the secretions are aspirated with a suction tube of 18 Fr of 6mmdiameter. When the tube is inserted into the endotracheal tube, before proceeding with the aspiration of the secretions, a capnometer is attached to its outer end (picture A), measuring the etCO2 value for 10-15 seconds. At the end of the measurement, we proceed with the aspiration of the secretions as usual.

[figure not shown]
Pic. A

We then proceed with the laying of an NGT according to local protocols. Also in this case, once the NGT has been inserted, the etCO2 is measured at the end of the probe (pic A) for 10-15 seconds and its value is recorded in the CRF. At the end of the measurement, the capnometer can be detached, as a standard procedure, and the NGT can be used as usual.

At the end of the procedure, therefore, for each patient, two values ​​of etCO2 are acquired which will allow to obtain two "populations of values" of the etCO2: the values recorded ​​at the endotracheal level and the one recorded at the esophageal level. Through statistical analysis, we will find the "threshold value" above which the value of etCO2 found is certain for a location in the trachea. The expected mean values of etCO2, according to the literature, are 40 mmHg in the trachea (range 35-45 mmHg) and <25mmHg in the esophagus.

Group B procedure:

The group B enrolment will start at the Regional Hospital of Bellinzona. The enrolled patients are sedated and intubated according to the clinical indications and the local protocols, independently from the ongoing study.

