Anaesthesia is performed by a professional anaesthesiologist and an anaesthetist nurse, using standardized procedures according to local routine protocols. At the end of the procedure, once the NGT is inserted, the pH is measured by aspirating the gastric contents and measuring on specific litmus paper the pH values, both at a distance of 25 cm from the mouth (esophageal site) and at a distance of 40 cm (gastric site).

At the end of the procedure, for each patient two values ​​of pH are acquired which will allow to obtain two pH "value populations": a value at esophageal level and a value at the gastric level. Through statistical analysis (see Section 6), we will try to find the "threshold value" below which the pH is suggestive for a localization in the gastric area.

The expected mean values of pH are 3.8 in the stomach (range 3.2-4.4) and 8.5 in the esophagus (range 6-9.5).

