## 6.2. Statistical analysis plan

We tabulate the distribution of baseline variables across the study sections, summarizing categorical variables by frequencies and percentage and numerical variables either by mean and standard deviations (±SDs), or by medians and interquartile ranges (IQR). Data distribution was verified using a Kolmogorov- Smirnov test.

We checked adherence to the protocol for each patient during the study. We assess and report total adherence rate to our protocol in order to analyse data on the intention-to-treat (ITT) and on the per-protocol (PP) population. Primary analysis is carried out on the ITT population for each study group, irrespective of potential non-adherence to the study protocol. Secondary analyses included analysis on the PP population, concerning the patients enrolled and treated following all the study procedures. The results of the performed analyses on the two populations are compared. All hypothesis tests are one-sided and considered significant if p-value is ≤ 0.01. Analyses are accomplished with the intention-to-treat if not otherwise specified.

In group A we tested the hypothesis of difference in the proportion of etCO2 level into the tracheal group and into the esophageal group (measurements collected in patients enrolled in group A), with the ITT. We executed a z-test for comparison of the two proportions, refusing the null hypothesis of no difference between the two if the p-value was ≤0.01. This to identify the threshold value of etCO2 above which tracheal location of NGT is determined with high precision. Similarly, in group B we tested the hypothesis of difference in the proportion of pH level into the esophageal and gastric group, with the ITT. We carried out a z-test for comparison of the two proportions, refusing the null hypothesis of no difference between the two if the p-value was ≤ 0.01. This to identify the threshold value of pH below which gastric location of NGT is determined with high precision. Statistical analysis was performed using SPSS version 10.0 (IBM, Chicago, IL, USA) for Mac OS.

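### The endpoint seeks a cut-off at which tube location is sure or certain, which 30 to 40 patients and a z-test cannot establish

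*Protocol*

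**What the plan says.** Protocol Section 4.1 gives group A the aim of finding "a threshold value of etCO2 above which we can be sure that aspiration probe is in the trachea", and group B is run "with the aim to find a threshold value of pH below which we can be certain that NGT is in the stomach". Section 4.3 repeats the strong form for group A: a value "above which the value of etCO2 found is certain for a location in the trachea".

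The strength of the claim varies elsewhere. For group B, Section 4.3 looks only for a value "below which the pH is suggestive for a localization in the gastric area". Section 6.2 says of its pH test: "This to identify the threshold value of pH below which gastric location of NGT is determined with high precision".

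The one method offered for finding either threshold is the test in Section 6.2: a one-sided z-test of two proportions at the 0.01 level, applied to the enrolled patients. No cut-off is named to define the proportions, and no error limit or validation step is described.

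On earlier evidence, Section 3.1 says a clinical trial "identified the cut off pH<5.5 to distinguish between the correct positioning in the stomach", while Section 3.2 says "there are no studies in this sense to identify the 'threshold level' below which the pH certainly appears to be a gastric" and non-oesophageal value. No analysis at 5.5 is described.

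**The concern.** A threshold that leaves no doubt about location is a claim about future patients: almost no reading from the wrong site may fall on the accepting side. Two features of the plan prevent that conclusion. The sample is small, so even a perfect result leaves an appreciable error rate possible. The cut-off is also chosen and assessed on the same readings, so its apparent performance is flattering.

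This matters because the synopsis and Section 8.2 foresee the thresholds making radiography unnecessary, and Section 3.1 calls radiography the gold standard. For pH the direction is direct: an oesophageal reading below the cut-off would be taken as gastric. An error-free sample is also a realistic outcome, because the ranges expected in Section 4.3 do not overlap (gastric pH 3.2 to 4.4 against oesophageal 6 to 9.5; tracheal etCO2 35 to 45 mmHg against oesophageal below 25 mmHg). Under the wording of Section 4.1, such a sample would invite a report of certainty.

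**Working it through.** **1. Numbers of patients (Section 6.1).** The base sizes are 35 (group A) and 30 (group B), with 10% loss. 35/0.9 = 38.9, so 39 (stated 40). 30/0.9 = 33.3, so 34 (stated 35). The inflation is in order. The base sizes cannot be reproduced, because the protocol gives no proportions or standard deviations. The argument does not depend on them.

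**2. What the z-test can show.** With a one-sided level of 0.01, 90% power and no continuity correction, two independent proportions of 0.95 and 0.60 need 35 per site, and 0.80 and 0.35 need 30. These pairs are illustrations and are not taken from the protocol. In the first, the test would very probably be significant at an etCO2 cut-off that 95% of tracheal and 60% of oesophageal readings exceed. A p-value of 0.01 or less is therefore compatible with gross misclassification.

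**3. What an error-free result can show.** Take a cut-off fixed in advance, with n wrong-site readings of which none crosses it. The exact upper limit p solves (1 − p)^n = a, so p = 1 − a^(1/n).

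| n | One-sided 95% (a = 0.05) | Two-sided 95% (a = 0.025) | One-sided 99% (a = 0.01) |
|---|---|---|---|
| 30 | 9.5% | 11.6% | 14.2% |
| 35 | 8.2% | 10.0% | 12.3% |
| 40 | 7.2% | 8.8% | 10.9% |

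The last column matches the protocol's own significance level. Conversely, n = ln(0.05)/ln(1 − p): with no errors, bounding the rate at 5%, 2% or 1% (one-sided 95%) takes 59, 149 or 299 patients.

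**4. What choosing the cut-off from the data adds.** The protocol gives no selection rule, so two are assumed.

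- *Cut-off at the most extreme wrong-site reading.* The apparent error is zero. The expected true error is 1/(n + 1): 1/31 = 3.2%, 1/36 = 2.8%, 1/41 = 2.4% for n = 30, 35 and 40. Its 95th percentile is about 9%, 8% and 7%.
- *Cut-off maximising sensitivity + specificity − 1 for pH.* This was simulated 4,000 times with independent normal readings, means 3.8 (Section 4.3) and 7 (Section 6.1), and an assumed common SD. At n = 30 the index averaged 0.92 in the sample against 0.87 in truth with SD 1, and 0.77 against 0.69 with SD 1.5. Results at n = 35 were nearly the same.

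**5. Whether pH 5.5 is worth testing.** Section 4.3 puts 5.5 between the two expected ranges (4.4 and 6). Section 6.1 assumes an oesophageal pH of about 7 with an interval of 5 to 8, which contains 5.5. On the protocol's own figures the question is open. Under the assumptions of step 4, a cut-off of 5.5 would give sensitivity and specificity of 96% and 93% (SD 1) or 87% and 84% (SD 1.5).

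**The case against.** The best defence is that Section 4.1 states an aim and no decision rule; that Sections 4.3 (group B) and 6.2 are more guarded; and that confidence limits, an external cut-off and the label given to a threshold can be left to an analysis plan or the report. Part of this stands. The method for an interval may well sit in an analysis plan, and the selection rules in step 4 are assumptions. But the endpoint wording is the protocol's own, it conflicts with the softer passages, and no choice of interval turns 30 to 40 patients into certainty.

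Several stronger readings are tempting and are not supported:

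- **That the protocol denies the 5.5 cut-off exists.** Section 3.2 denies only studies giving a level at which pH is certainly gastric and non-oesophageal. This sits awkwardly beside Section 3.1, but both can be true.
- **That 25 mmHg is a second cited cut-off.** Sections 3.1 and 4.3 give it as the value expected in the oesophagus, not as a published dividing line.
- **That the possible error is several times the roughly 1% complication rate of Section 3.1.** That rate is per insertion; the limits here are conditional on a wrong-site reading. If 1% to 5% of tubes were misplaced (an assumption), an 8% conditional error would be 0.08% to 0.4% of insertions.
- **That the group A limit measures missed airway placements.** A wrong-site reading above the etCO2 cut-off is an oesophageal reading called tracheal, a false alarm. A missed airway placement is a tracheal reading below the cut-off and needs its own count.
- **That the synopsis promises certainty.** It speaks only of finding threshold values.

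**Conclusion.** The point holds as a mismatch between the claim sought and what the design can deliver. With no observed error at a pre-set cut-off, the one-sided 95% upper limit on the wrong-site rate is 9.5% for the 30 evaluable patients of group B, 8.2% for the 35 of group A, and 7.2% if all 40 enrolled in group A are usable. These limits assume one independent reading per patient and site, and no distribution. They are the favourable case: a data-picked cut-off carries optimism as well, of a size that depends on a selection rule the protocol does not state. The z-test supplies no limit at all. It does not follow that the study will report a zero error rate, or that the resulting threshold will be poor; only that certainty cannot be concluded from it.

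**What to change.** - In Section 4.1 and the group A text of Section 4.3, replace the language of being sure or certain with an estimated misclassification rate and its exact 95% upper bound. Bring this into line with the group B text of Section 4.3 and with Section 6.2, so that one strength of claim runs through the protocol.
- For etCO2, report both errors: oesophageal readings above the cut-off and tracheal readings below it.
- For pH, add a pre-specified evaluation of the cut-off below 5.5 cited in Section 3.1: the proportions of oesophageal and of gastric readings below it, each with an exact interval. This is an analysis of a fixed value, not a recommendation to use it.
- Label any threshold derived from these data as exploratory pending validation.
- In Section 3.2, say how the cited 5.5 relates to the evidence gap claimed, so that it agrees with Section 3.1.

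The synopsis needs no change on this point. No further patients or measurements are required; the cost is wording, a few extra proportions and a weaker claim than certainty.

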## 4.2 Study design

This is a prospective, multisite, observational, physiological study, which aims to identify two groups of values ​​regarding the measured etCO2 in the trachea and esophagus (group A group) and regarding the measured pH in the esophagus and stomach (group group B).

This study aims to be a study, taking advantage of two methods already used in clinical daily life (such as capnometry and pH measurement with litmus paper) to identify "reference values".

The study will involve two sites located in the Canton Ticino (Switzerland): the Regional Hospital of Bellinzonaand Clinica Luganese Moncucco.

Group A will be done entirely in the Clinica Luganese Moncucco while group B in the Regional Hospital of Bellinzona. In this way, the staff training will be more easily practicable. Possible bias will be avoid as the measurement in each centers will be perfomed with more than one device. The devices are calibrated by external facilities according to the international standards.

Moreover, all the staff will be involved measurement collection as the survey is not operator-based.

Inclusion and exclusion criteria will be the same for Group A and Group B patients.

This study will not interfere with the patient’s routine treatment and there will be no deviation from the standard of care. All the procedures of parameters survey will take place just once, during patient access to the ICU.

Upon study inclusion, all the parameters will be collected during the standard procedures of NGT positioning (see next paragraph for further details).

## 4.3 Study intervention

Group A procedure:

Patients needing the installation of a NGT at the Clinica Luganese Moncucco are consecutively enrolled and selected according to the inclusion and exclusion criteria listed below. The enrolled patients, after receiving adequately protocol study explanation and signed the informed consent, are sedated and intubated according to the clinical indications and the local protocols, independently from the ongoing study.

Anaesthesia is performed by a professional anaesthesiologist and an anaesthetist nurse, using standardized procedures according to local routine protocols. Induction and intubation therefore take place independently of the ongoing clinical study, independent from both indications for intubation, the choice of drugs and intubation material. At the end of the procedure, as usual, the secretions are aspirated with a suction tube of 18 Fr of 6mmdiameter. When the tube is inserted into the endotracheal tube, before proceeding with the aspiration of the secretions, a capnometer is attached to its outer end (picture A), measuring the etCO2 value for 10-15 seconds. At the end of the measurement, we proceed with the aspiration of the secretions as usual.

[figure not shown]
Pic. A

We then proceed with the laying of an NGT according to local protocols. Also in this case, once the NGT has been inserted, the etCO2 is measured at the end of the probe (pic A) for 10-15 seconds and its value is recorded in the CRF. At the end of the measurement, the capnometer can be detached, as a standard procedure, and the NGT can be used as usual.

At the end of the procedure, therefore, for each patient, two values ​​of etCO2 are acquired which will allow to obtain two "populations of values" of the etCO2: the values recorded ​​at the endotracheal level and the one recorded at the esophageal level. Through statistical analysis, we will find the "threshold value" above which the value of etCO2 found is certain for a location in the trachea. The expected mean values of etCO2, according to the literature, are 40 mmHg in the trachea (range 35-45 mmHg) and <25mmHg in the esophagus.

Group B procedure:

The group B enrolment will start at the Regional Hospital of Bellinzona. The enrolled patients are sedated and intubated according to the clinical indications and the local protocols, independently from the ongoing study.

Anaesthesia is performed by a professional anaesthesiologist and an anaesthetist nurse, using standardized procedures according to local routine protocols. At the end of the procedure, once the NGT is inserted, the pH is measured by aspirating the gastric contents and measuring on specific litmus paper the pH values, both at a distance of 25 cm from the mouth (esophageal site) and at a distance of 40 cm (gastric site).

At the end of the procedure, for each patient two values ​​of pH are acquired which will allow to obtain two pH "value populations": a value at esophageal level and a value at the gastric level. Through statistical analysis (see Section 6), we will try to find the "threshold value" below which the pH is suggestive for a localization in the gastric area.

The expected mean values of pH are 3.8 in the stomach (range 3.2-4.4) and 8.5 in the esophagus (range 6-9.5).

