| **Endpoints** | Group A:  - the aim is to find a threshold value of etCO2 collected when the NGT is well positioned in trachea;  Group B  - the aim is to find a threshold value of pH collected when the NGT is positioned in the esophagus and in the stomach  Secondary endpoints:   - Group A: identify patients suffering from chronic obstructive pulmonary disease (COPD) and perform a sub-analysis to identify the threshold value; - Group B: identify patients taking proton pump inhibitors (PPIs) and perform a sub-anaysis to identify the threshold value in case of an already diagnosed gastro-esophageal reflux disease. |
| **Inclusion- / Exclusion Criteria** | Inclusion criteria:  • Adult patients (> 18 years)  • Patients male and female  • Patients intubated by oro- or naso-tracheal way  • Post-induction curarized patients  • Fasting patients (from at least 6 hours)  Exclusion criteria:  • Patient refusal  • Patients with known bleeding diathesis / ongoing bleeding  • Patients at risk of bleeding (defined as thrombocytes <50 G/l, INR> 2.5, aPTT> 70 sec)  • Patients with traumatic brain injury / Polytrauma  • Patients with esophagus-tracheal fistulas or malformations of the ENT sphere  • Patients with current or previous radiotherapy of the ENT sphere  • Patients unable to give their informed consent due to language barriers  • Women who are pregnant |
| **Procedures and Assessments** | Clinical data will be collected at the NGT positioning |
| **Number of Participants with Rationale** | The study will include a total number of 75 patients (group A: 40 pts, group B: 35 pts) |
| **Study Duration and Schedule** | Planned 01/2020 of First-Participant-In  Planned 01/2021 of Last-Participant-Out |

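### Group A reads the trachea only through a suction tube and the comparison site only through an NGT, so the threshold is not shown to apply to an NGT in the airway

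*Protocol*

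**What the plan says.** Protocol section 4.3 fixes two readings per group A patient, in a fixed order.

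- **Tracheal reading.** After intubation, "the secretions are aspirated with a suction tube of 18 Fr of 6mmdiameter". The reading is made through this tube while it lies within the endotracheal tube and suction has not yet begun: "a capnometer is attached to its outer end (picture A), measuring the etCO2 value for 10-15 seconds".
- **Second reading.** "We then proceed with the laying of an NGT according to local protocols". Then, "once the NGT has been inserted, the etCO2 is measured at the end of the probe (pic A) for 10-15 seconds". The NGT is afterwards used in the ordinary way. No calibre or insertion depth is given for group A, and the value is labelled oesophageal.

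The target of the threshold is stated in three places:

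- Synopsis, Endpoints: "the aim is to find a threshold value of etCO2 collected when the NGT is well positioned in trachea".
- Section 6.2: "This to identify the threshold value of etCO2 above which tracheal location of NGT is determined with high precision".
- Section 4.1: a value above which an aspiration probe, not an NGT, is sure to be in the trachea.

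Section 4.2 says bias is avoided because each centre measures with more than one device and the devices are externally calibrated. The synopsis (Risk / Benefit Assessment) and section 8.2 foresee the thresholds as predictors of correct NGT placing that could spare the radiograph.

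**The concern.** The planned comparison is presented as one between two anatomical sites. As executed, it is also a comparison between two tubes. Every tracheal value comes from a suction tube within the endotracheal tube, and every other value comes from an NGT. If the tube affects the reading, that effect is absorbed into the apparent difference between sites and into the cut-off derived from it.

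The use foreseen in section 8.2 is to judge where an NGT lies. A reading below the cut-off would then reassure. That reassurance depends on how often an NGT in the airway would read above the cut-off, which the study does not observe. Because the gap arises when the data are collected, no later analysis plan can close it.

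The label of the second reading raises a related question. If the tip is already in the stomach when the value is taken, the study contrasts trachea with stomach, not with oesophagus.

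**Working it through.** **1. Which combinations are observed.** From section 4.3:

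| | Trachea | Oesophagus, or wherever the inserted NGT ends |
|---|---|---|
| Suction tube, 18 Fr | read in every patient, inside the endotracheal tube | never read |
| NGT, calibre not stated | never read | read in every patient |

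Write a reading as patient effect + site effect + tube effect. The within-patient difference is then (site: trachea − comparison) + (tube: suction − NGT). Only this sum is estimated, whether 35 or 40 patients contribute. The endotracheal lumen and the order of the readings change together with site in the same way. Using several calibrated devices (section 4.2) does not fill either empty cell.

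**2. Which property of the threshold is affected.** For a cut-off c and an NGT as the tube being judged:

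- Sensitivity = P(reading > c, given an NGT in the trachea). This needs the empty cell at the lower left.
- Specificity = P(reading ≤ c, given an NGT not in the trachea). This uses the lower right cell, which is observed through a real NGT, subject to step 4.

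So the substitution of tubes bears mainly on sensitivity.

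**3. Endpoint statements side by side.** The synopsis and section 6.2 name the NGT in the trachea; section 4.1 names the aspiration probe. The procedure in section 4.3 can serve only the section 4.1 wording. The statements must be reconciled whatever the size of a tube effect.

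**4. The label of the second reading.** Section 4.3 gives no depth for group A. The reading follows insertion, and the tube is then ready for use. Group B, in the same section, distinguishes an oesophageal site at 25 cm from a gastric site at 40 cm, also measured after insertion. The text therefore leaves open that the group A tip is gastric, and does not establish it.

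**5. Can the effect be sized?** The documents give no tube offset b, no cut-off c and no SD. Purely on assumptions, with normal tracheal readings of mean 40 mmHg (sections 4.3 and 6.1), the share of airway NGTs reading below c is Φ((c − (40 − b))/SD). Two SDs can be read from the documents: 30–50 in section 6.1 as a 95% range gives 10/1.96 = 5.10; 35–45 in section 4.3 read the same way gives 5/1.96 = 2.55.

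- b = 0, c = 30, SD 5.10: Φ(−1.96) = 2.5%
- b = 5, c = 30, SD 5.10: Φ(−0.98) = 16%
- b = 5, c = 30, SD 2.55: Φ(−1.96) = 2.5%
- b = 5, c = 25, SD 5.10: Φ(−1.96) = 2.5%
- b = 10, c = 30, SD 5.10: Φ(0) = 50%

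The result follows the chosen inputs, so none of these figures is evidence about this study. The planned group A size has no bearing on the point.

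**The case against.** The strongest defence is that the surrogate follows from the setting. This is a category A observational study that promises no departure from standard care (section 4.2) and only the risk of ordinary NGT placing (section 8.2). Putting an NGT into the airway on purpose would not fit. Routine suction offers a tracheal value at no added burden. That justifies the measurement; it does not justify wording the conclusion for a tube that was not measured.

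Second, section 3.2 puts the emphasis on specificity, and the false positive rate rests on readings taken through a real NGT. This stands and narrows the point to sensitivity. The use foreseen in section 8.2 still needs both.

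Third, the choice of NGT is left to local protocols, so an unstated calibre is not an error in itself. This also stands; the calibre need only be recorded. Both readings refer to the same picture, which is not shown, so no difference in the capnometer connection can be asserted either.

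Fourth, under the section 4.1 wording the tracheal readings match their target. That is true, but it conflicts with the synopsis and section 6.2.

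**Conclusion.** The point holds as a limit on what group A can conclude. Tube and site coincide in every patient, two of the three endpoint statements describe a condition that is never measured, and the oesophageal label is not supported by a stated depth. This rests on the text of the protocol alone and needs no numerical assumption.

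A reader might go further in three ways that the documents do not support:

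- That the threshold fails for an NGT in the trachea. No size or direction of a tube effect is given and it may be near zero; the threshold is only not shown to apply.
- That the second reading is certainly gastric. The depth is unspecified; gastric is a possibility suggested by the sequence.
- That a particular share of misplaced tubes would be missed. Any such share depends on an invented cut-off, SD and offset, so no magnitude is claimed.

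**What to change.** 1. Reconcile the synopsis (Endpoints), section 4.1 and section 6.2 so that all three name the same tube.
2. In those places, and in the synopsis statements on statistics and on risk and benefit and in section 8.2, limit the group A conclusion to a suction tube within the endotracheal tube versus an NGT in situ. State the difference in tubes as a limitation.
3. Add NGT calibre and insertion depth to the CRF for group A.
4. Either take the second reading at a stated oesophageal depth, if that is compatible with standard care at the site, or relabel it *NGT in final position* wherever it is named. Group B is a precedent for stating a depth. It is not a precedent for reading during insertion, because its pH values are taken once the tube is in.

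Reading both sites through the same tube would remove the confounding, but it could conflict with the commitment in section 4.2 to leave care unchanged, so it is not required here.

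The cost is a narrower claim and two CRF fields, with no additional patients. A reading at a stated depth, if chosen, would add a step to the procedure; relabelling would not.
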